Study protocol of the effect of low-dose esketamine on the quality of early recovery in patients undergoing laparoscopic radical resection of colorectal cancer

**Applicant :** [name]

**[contact]

**Department :** Department of Anesthesiology, Pain and Perioperative Medicine, The First Affiliated Hospital of Zhengzhou University

**Contact :** [name]

**[contact]

1. **Basis for project approval**

Colorectal cancer (CRC) is a common clinical malignant tumor. With the change of living habits and diet structure, the incidence of CRC has been increasing in recent years^[1]^. Currently, CRC is mainly treated by comprehensive methods based on surgical resection. Compared with traditional open surgery, laparoscopic radical surgery is minimally invasive and has fewer postoperative complications, which has become a common surgical method in clinical practice^[2]^. To a certain extent, it accelerates postoperative recovery, which is consistent with the concept of enhanced recovery after surgery (ERAS). ERAS advocates the use of a series of optimized perioperative treatment measures confirmed by evidence-based medicine to minimize the psychological and physiological stress response of patients, so as to accelerate the recovery of patients^[3]^. Among them, anesthesia management to promote postoperative rehabilitation is also an important part of ERAS. Improvements in interventions to evaluate patient experience after anesthesia and surgery require a special emphasis on patient-centered outcome assessment^[4]^. Anesthesiologists should use effective methods during the perioperative period (optimizing preoperative, intraoperative and postoperative patient management, etc.) to reduce the noxious stimulus response to surgery and complications, and improve the quality of recovery, so as to shorten the length of stay in PACU and hospital, reduce the consumption of medical resources, and improve the satisfaction and quality of life of patients^[5,6]^. As anesthesiologists, we have a responsibility to optimize the postoperative experience and identify techniques that provide rapid, high-quality recovery while minimizing morbidity and time to return to daily activities^[7]^. The choice of perioperative anesthetic drugs and techniques is an important factor affecting the postoperative recovery of patients^[8]^.

Esketamine is the dextroversion of ketamine, mainly acts on N-methyl-D-aspartate (NMDA) receptor, non-competitively inhibits the activation of the receptor by glutamine, and has a time-dependent and frequency-dependent block of NMDA, so as to weaken neuronal activity and produce anesthetic and analgesic effects^[9]^. And, its potency is twice that of ketamine, which leads to stronger sedative and analgesic effects, and a lower incidence of adverse reactions than ketamine^[10]^. Previous studies have shown that ketamine, as an NMDA receptor, can provide good analgesic effect, and reduce central sensitization and hyperalgesia when combined with opioids, thereby reducing the dosage of opioids and their related side effects^[11,12]^. Moreover, esketamine has a high clearance rate and rapid metabolism in human body, which increases the controllability of anesthesia, and makes patients awake faster and safer^[13]^.

Ketamine has an anti-inflammatory effect, which can reduce the levels of IL-1β, TNF α, IL-6 and other inflammatory factors in human peripheral blood^[14-16]^. The inflammasome is a protein complex that comprises an intracellular sensor, typically a Nod-like receptor (NLR), the precursor procaspase-1, and the adaptor ASC; and has a variety of subtypes, among which NLRP3 is the most widely studied^[17,18]^. Studies have proved that NLRP3 inflammasome is related to the level of pain, inflammation, and depression^[19-21]^. NLRP3 inflammasome can promote the maturation and secretion of IL-1β and IL-18, and play an important regulatory role in the inflammatory response of the body^[22]^. However, whether ketamine or esketamine can regulate the level of inflammation in the body through NLRP3 inflammasome, reduce postoperative pain, and improve postoperative recovery of patients is still unclear. At present, there are few ketamine studies on the quality of recovery with inconsistent results, and there is a lack of research on the effect of esketamine on the early quality of recovery^[23-25]^. Therefore, this trial is required.

**2. Objective and implication**

This study aims to observe the effect of low-dose esketamine on the early postoperative quality of recovery in patients undergoing laparoscopic radical resection of colorectal cancer and whether it can regulate the level of inflammation through NLRP3 inflammasome, reduce postoperative pain, and improve postoperative recovery of patients, so as to provide reference for the rational use of esketamine in total intravenous anesthesia.

**3. Content of the study**

3.1 Grouping

This is a prospective, randomized controlled trial. Patients will be randomly assigned in a 1:1 ratio to esketamine group (K group) and control group (C group) using a random number table method. In the K group, a loading dose of 0.25mg/kg of esketamine will be given after anesthesia induction, and then a rate of 0.12mg/kg/h will be continuous infusion until the end of surgery. The equal volume of normal saline will be infused in the C group.

(The above doses will be used in accordance with the actual clinical use of drugs or guidelines)

3.2 Inclusion and exclusion criteria

(1) Inclusion criteria

1) Patients scheduled for elective laparoscopic radical resection of colon cancer under general anesthesia;

2) Patients who will be to be anesthetized according to the two clinical anesthesia management protocols ;

3) American Society of Anesthesiologists (ASA) physical status Ⅰ-Ⅱ;

4) Patients aging from 18 to 65 years, no gender limit;

5) BMI of 18-30 kg/m^2^;

6) Written informed consent for anesthesia.

(2) Exclusion criteria

1) Refusal to participate in the study;

2) Contraindications to esketamine, such as glaucoma, large vessel aneurysm, etc.;

3) Preoperative use of sedative or analgesic drugs;

4) Severe cardiopulmonary, liver and kidney dysfunction;

5) Cognitive impairment or a history of psychiatric or neurological disorders.

(3) Elimination

1) Conversion to laparotomy;

2) The bleeding volume was more than 500ml;

3) A large amount of subcutaneous emphysema during the operation or hypercapnia after operation could not be corrected in a short time;

4) Severe postoperative complications affected the quality of postoperative recovery;

5) Patients are lost follow-up;

6) The surgical procedure is Miles.

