3.4 Outcomes

(1) Primary outcome

The primary outcome of this study is quality of recovery at 24 h after surgery, and it is assessed using the QoR-15 scale. The QoR-15 will be evaluated at three timepoints: before(T_before_), 24h(T_24h_) and 72h(T_72h_) after surgery.

(2) Secondary outcomes

1) The levels of NLRP3, IL-1β and IL-18 will be recorded at T0, T1, T3 and T4;

2) The duration of sugery, consumption of remifentanil, cisatracurium [dosage](javascript:;), application of vasoactive drugs;

3) MAP (mean arterial pressure) and HR will be recorded at before induction (T_0_), after the establishment of carbon dioxide pneumoperitoneum (T_1_), after closing the carbon dioxide pneumoperitoneum (T_2_), and at the end of surgery (T_3_);

4) Rescue analgesia during PACU, respiratory recovery time (the duration of time from withdrawal of anesthetics to return of spontaneous breathing), response time (the duration of time from withdrawal of anesthetics to a verbal command), extubation time (the duration of time from withdrawal of anesthetics to extubation).

5) VAS pain scores at rest (VAS-R) and on coughing (VAS-M) at 4h, 8h, 12h, 24h and 48h postoperatively; times of effective PCIA press at 24h and 48h after operation, the consumption of oxycodone, the use of additional analgesic drugs.

6) Hospital stay durations, intestinal function recovery time (the duration of time from extubation to the first exhaust time), time of first eating or drinking (the duration of time from extubation to the first drinking or eating time), ambulation time (the duration of time from extubation to the first bed time standing or walking), and adverse events such as nausea, vomiting, dizziness, hallucination and nightmare,etc.

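### The Elimination list removes randomised, dosed patients for later events, one of them defined by its effect on the primary outcome, so the QoR-15 comparison is biased if these events differ by arm

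*Protocol*

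**What the plan says.** Protocol section 3.2 has three lists: inclusion, exclusion and, separately, Elimination. Items 1 to 4 of the third list are "Conversion to laparotomy"; "The bleeding volume was more than 500ml"; "A large amount of subcutaneous emphysema during the operation or hypercapnia after operation could not be corrected in a short time"; and "Severe postoperative complications affected the quality of postoperative recovery". Item 5 is "Patients are lost follow-up", and item 6 is the Miles procedure.

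Section 3.1 sets the timing of treatment: "a loading dose of 0.25mg/kg of esketamine will be given after anesthesia induction", followed by an infusion to the end of surgery, with saline in the control group. Section 3.4 states: "The primary outcome of this study is quality of recovery at 24 h after surgery". Adverse events are a secondary outcome in the same section.

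Sections 2 and 4 give the hypothesis that esketamine alters inflammation and pain and improves recovery. Section 3.6 has a single follow-up researcher who does not know the allocation. Nothing in the protocol returns eliminated patients to any comparison.

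**The concern.** Randomisation makes the two groups comparable at the moment of allocation. That protection is kept only if what happens after dosing does not decide who is analysed. Items 1 to 4 cannot be known until the study infusion has started, so each removes a patient who has already been randomised and treated.

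Item 4 is the clearest fault. Its trigger is a severe complication that impaired recovery, and recovery is what the primary outcome measures. A trial that expects esketamine to improve recovery cannot also assume that complications which impair recovery are unrelated to the arm. If they are related, the 24 h QoR-15 difference describes selected patients and departs from the difference among those randomised. The terms that trigger items 3 and 4 (how severe, how soon corrected) are also undefined, which leaves room for discretion.

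**Working it through.** **Timing.** Drug or saline starts after induction (section 3.1). Conversion, blood loss, emphysema or hypercapnia, and postoperative complications all come later. Items 1 to 4 are therefore post-treatment events, and item 4 is worded through its effect on the primary construct.

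**The plan's own figure.** Section 3.7 gives a difference of 8.0 points, two-sided α 0.05, 80% power and 42 per group, but no SD. From n = 2(1.960 + 0.842)² × SD² / 8.0², an SD of 13 gives 2 × 7.85 × 169 / 64 = 41.5, rounded up to 42. SDs of 12.93 to 13.08 all give 42 (12.78 to 12.93 with the t distribution). I use 13 as an assumption. Enrolment is 46 per group.

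**Bias formula.** Let an eliminated complication lower the score by D points and occur at rates pK (esketamine) and pC (control). Let d be the treatment difference among patients without it.

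- All randomised patients: d − D(pK − pC)
- After elimination: d
- Bias (eliminated minus all): D(pK − pC)

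D, pK and pC are not in the protocol. The values below are assumptions.

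| pK vs pC | D = 20 | D = 30 | D = 40 |
|---|---|---|---|
| 5% vs 5% | 0 | 0 | 0 |
| 10% vs 5% | +1.0 | +1.5 | +2.0 |
| 15% vs 5% | +2.0 | +3.0 | +4.0 |
| 5% vs 10% | −1.0 | −1.5 | −2.0 |
| 5% vs 15% | −2.0 | −3.0 | −4.0 |

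A positive sign favours esketamine: the arm that loses more patients looks better. Against the 8.0-point MCID, 1.5 points is 19% and 3.0 points is 37.5%.

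**Type I error.** Set d = D(pK − pC), so that there is no true difference among all randomised patients, and apply the t-test (46 per arm, SD 13, 8,000 simulated trials per row).

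| D; pK vs pC | All kept | After elimination |
|---|---|---|
| 30; 5% vs 5% | 4.9% | 5.1% |
| 30; 10% vs 5% | 4.6% | 8.4% |
| 30; 15% vs 5% | 4.9% | 18.0% |
| 40; 15% vs 5% | 4.9% | 27.6% |

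Hand check of the third row: 46 × 0.85 = 39.1 and 46 × 0.95 = 43.7 patients remain. The standard error is 13 × √(1/39.1 + 1/43.7) = 2.86, and 3.0 / 2.86 = 1.05. The chance of exceeding ±1.96 is then about 18%.

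**Power.** At SD 13, removing 10%, 15% or 20% of 46 per arm leaves power of 80.0%, 77.7% or 75.2%. This is minor beside the bias.

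**The case against.** The best defence is that the bias needs arms that differ. With equal rates and equal penalties it is zero, follow-up is blinded, and controls receive an equal volume of saline. Patients are 18 to 65 years old, ASA I–II and without severe organ dysfunction, so severe complications may be few. At a 30-point penalty, one extra elimination in one arm moves the difference by only 30 / 46 = 0.65 points, about 8% of the MCID. All of this stands as a limit on size. It does not rescue the rule: blinding restrains group-driven judgement, but it does not help when treatment changes how often the event occurs.

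Four stronger readings are tempting, and the text does not carry them.

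- A reader might infer that item 4 removes anyone who recovers poorly. It does not: a patient with a low QoR-15 and no severe complication stays in.
- A reader might infer that severe complications are dropped from the safety comparison. The protocol never says which analyses elimination applies to, and a SAP could define a safety set. What can be said is that the wording allows such events to go uncounted.
- A reader might infer that a patient with a 24 h score who misses only the 72 h visit is eliminated. Item 5 has no time limit, but it could equally mean that no 24 h score exists.
- A reader might treat all six items as outcome-related. The documents do not show that the drug affects conversion or blood loss. The Miles procedure is a type of surgery, and loss to follow-up is a missing-data matter.

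An unseen SAP may also hold the analysis sets and missing-data methods. The objection here is to an explicit rule in the protocol that removes treated patients, not to missing detail.

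**Conclusion.** The point holds and should be corrected before the primary analysis. Items 1 to 4 remove treated patients on post-randomisation events, and item 4 does so on a criterion tied to the primary outcome.

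Neither the sign nor the size of the bias can be known from the protocol. Over the assumed rates of 5% to 15% and penalties of 20 to 40 points it runs from 0 to 4.0 points in either direction. The 30-point cases give 1.5 and 3.0 points, with type I error of about 8% and 18% instead of 5%. These figures rest on an SD of about 13, which is back-solved, and on rates and penalties that are illustrations only. If esketamine lowered the complication rate, the same rule would hide part of its benefit. For adverse events, the conclusion is limited to an ambiguity that needs to be closed.

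**What to change.** Replace the Elimination list with an analysis rule:

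- Analyse all randomised patients who received esketamine or saline, in their assigned group, for the 24 h QoR-15 and for adverse events, whether or not an event in items 1 to 4 occurs. Report by arm anyone randomised who never started the infusion.
- Collect the 24 h QoR-15 regardless of these events, and report the events by arm.
- Keep the eliminated set only as a labelled sensitivity analysis.
- Treat loss to follow-up as missing data at the affected time point, not as removal of the patient.
- Apply the Miles criterion before randomisation where that procedure is planned; otherwise keep the patient in the main analysis.

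The cost is mainly wording, plus collecting the 24 h score in patients who would now be dropped. Variance will be somewhat larger and the estimated effect may be smaller. Section 3.7 describes enrolment in the past tense. If recruitment has ended, the analysis rule and the by-arm reporting can still be changed, using whatever scores were collected.

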3.3 Methods

(1) Preoperative visit

All patients to be included in the study will be interviewed before surgery, focusing on whether the patient had a history of anesthesia, neurological or psychiatric system diseases, heart, brain, liver and kidney diseases, and long-term use of sedative and analgesic drugs. The relevant blood test data and imaging examination results of the patients will be reviewed. The physical examination of the patients will be performed, and the preoperative examination will be improved to determine whether there will be a difficult airway. The ASA classification and cardiac function classification of the patients will be comprehensively evaluated. The patients will be told to strictly fast for 8 hours and drink for 2 hours before surgery. The patients and their families will be informed of the possible anesthetic complications and accidents during the perioperative period, and the informed consent of anesthesia will be signed. The content and clinical significance of this study will be explained to the patients and their families. Informed consent for this study will be signed by the patients or their proxies after consent was obtained.

(2) Preparation before anesthesia

After patients enter the operation room, peripheral venous access will be opened and electrocardiogram (ECG), non-invasive blood pressure (NBP), heart rate (HR), pulse oxygen saturation (SpO_2_), and the bispectral index (BIS) will be monitored. The radial artery and right internal jugular vein will be punctured and catheterized under local anesthesia.

(3) Management of anesthesia

A rapid intravenous induction method will be used. After adequate preoxygenation, all patients will be induced for general anesthesia by intravenous injection of 0.2-0.3mg/kg etomidate, 0.5-1.0μg/kg sufentanil, 0.15-0.3mg/kg cisatracurium, and will maintain with 4-12mg/kg/h propofol and 0.05-2ug/kg/min remifentanil after intubation. The BIS value of the subjects will be maintained between 40 and 60 by adjusting the infusion rate of propofol during surgery. Oxygen and air inhalation flow will be set as 1L/min, V_T_ 6-8 ml/kg,RR 12-16 times/min,I:E=1:2 and P_ET_CO_2_ 35-45 mmHg（1mmHg=0.133kPa）. Intermittent intravenous injection of cisatracurium will be used to maintain muscle relaxation during surgery. Vasoactive drugs will be used to regulate hemodynamic stability when necessary. In the K group, a loading dose of 0.25mg/kg of esketamine will be given after anesthesia induction, and then a rate of 0.12mg/kg/h will be continuous infusion until the end of surgery. The equal volume of normal saline will be infused in the C group. The levels of NLRP3, IL-1β and IL-18 will be measured before induction (T0), after establishment of CO2 pneumoperitoneum (T1), at the end of surgery (T3) and on the first day after surgery (T4).

Palonosetron, 0.25mg, will be intravenously injected to prevent nausea and vomiting, and sufentanil, 0.1-0.2 μg/kg, will be used for analgesia about 30 minutes before the end of surgery. All anesthesia maintenance drugs will be discontinued after finishing skin closure. At the end of surgery, all patients in the two groups will be given a patient-controlled intravenous analgesia pump (PCIA,200ml) consisting of oxycodone 0.6mg/kg and palonosetron 0.25mg for 48h after surgey. The background infusion rate will be 3ml/h, single additional dose will be 4ml, the locking time will be 15min, and there will be no initial infusion dose.

After the operation,all patients will be transferred to the post anesthesia care unit (PACU). During the stay in PACU, oxycodone 0.05-0.1 mg/kg will be injected intravenously for rescue analgesia when the VAS score will be ≥ 4. The endotracheal tube will be removed when the patient become conscious and the tidal volume and muscle strength have returned to preoperative levels.

3.4 Outcomes

(1) Primary outcome

The primary outcome of this study is quality of recovery at 24 h after surgery, and it is assessed using the QoR-15 scale. The QoR-15 will be evaluated at three timepoints: before(T_before_), 24h(T_24h_) and 72h(T_72h_) after surgery.

(2) Secondary outcomes

1) The levels of NLRP3, IL-1β and IL-18 will be recorded at T0, T1, T3 and T4;

2) The duration of sugery, consumption of remifentanil, cisatracurium [dosage](javascript:;), application of vasoactive drugs;

3) MAP (mean arterial pressure) and HR will be recorded at before induction (T_0_), after the establishment of carbon dioxide pneumoperitoneum (T_1_), after closing the carbon dioxide pneumoperitoneum (T_2_), and at the end of surgery (T_3_);

4) Rescue analgesia during PACU, respiratory recovery time (the duration of time from withdrawal of anesthetics to return of spontaneous breathing), response time (the duration of time from withdrawal of anesthetics to a verbal command), extubation time (the duration of time from withdrawal of anesthetics to extubation).

5) VAS pain scores at rest (VAS-R) and on coughing (VAS-M) at 4h, 8h, 12h, 24h and 48h postoperatively; times of effective PCIA press at 24h and 48h after operation, the consumption of oxycodone, the use of additional analgesic drugs.

6) Hospital stay durations, intestinal function recovery time (the duration of time from extubation to the first exhaust time), time of first eating or drinking (the duration of time from extubation to the first drinking or eating time), ambulation time (the duration of time from extubation to the first bed time standing or walking), and adverse events such as nausea, vomiting, dizziness, hallucination and nightmare,etc.

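### First flatus, first intake and ambulation are timed from extubation, so any between-arm difference in extubation time is subtracted from all three; the direction is unknown and the likely size small.

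*Protocol*

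**What the plan says.** Protocol section 3.4, secondary outcomes item 6, gives three durations the same starting point:

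- bowel function: "intestinal function recovery time (the duration of time from extubation to the first exhaust time";
- oral intake: "time of first eating or drinking (the duration of time from extubation to the first drinking or eating time";
- mobilization: "ambulation time (the duration of time from extubation to the first bed time standing or walking".

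Item 4 of the same list makes the time of extubation an outcome: "extubation time (the duration of time from withdrawal of anesthetics to extubation". The other two emergence times in item 4, return of spontaneous breathing and response to command, also run from withdrawal of anesthetics.

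Section 3.3, under management of anesthesia, sets the condition for extubation: "The endotracheal tube will be removed when the patient become conscious and the tidal volume and muscle strength have returned to preoperative levels". The same part gives the esketamine group a loading dose, after which "a rate of 0.12mg/kg/h will be continuous infusion until the end of surgery"; controls receive saline. It also stops the anesthetic maintenance drugs once the skin is closed.

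On how the drug affects waking, section 1 points two ways. Esketamine's potency relative to ketamine is one "which leads to stronger sedative and analgesic effects", but its rapid clearance "makes patients awake faster and safer".

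**The concern.** A time-to-recovery outcome in a randomized trial should start from a point that treatment cannot move. Extubation is not such a point. It comes after randomization and requires consciousness, and one arm alone receives a centrally acting drug up to the end of surgery. The protocol treats extubation time as something the drug may change, since it compares it between arms.

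Take two patients whose anesthetics stop at the same moment and who first drink at the same clock time. The one extubated later is recorded as having the shorter time to first intake. The three outcomes then measure recovery net of emergence, whereas section 2 asks about postoperative recovery. At stake are the size, and for an outcome with a small spread possibly the significance, of three secondary comparisons.

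**Working it through.** **Inputs from the protocol.** The three item 6 times start at extubation; extubation time in item 4 starts at withdrawal of anesthetics (both section 3.4). The calculated sample size is 42 per arm with a two-sided 5% test (section 3.7). The protocol states no extubation, intake, ambulation or flatus times and no spread for them, so there is no figure of its own to reproduce on this point.

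**Step 1, the identity.** For each patient:

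(extubation to event) = (withdrawal to event) − (withdrawal to extubation)

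Taking means and subtracting control from esketamine:

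difference as defined = difference from withdrawal − difference in extubation time

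The shift equals the between-arm difference in mean extubation time with its sign reversed, and it is the same number of minutes for all three outcomes. If esketamine patients are extubated d minutes later, each of their mean recovery times looks d minutes shorter. If d minutes earlier, each looks d minutes longer.

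**Step 2, relative size.** Assumptions: a 5 to 20 minute difference in extubation time, first intake at 4 to 6 h (240 to 360 min), first flatus at 24 to 48 h (1440 to 2880 min).

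| Outcome | Smallest shift | Largest shift |
|---|---|---|
| First intake | 5/360 = 1.4% | 20/240 = 8.3% |
| First flatus | 5/2880 = 0.2% | 20/1440 = 1.4% |

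**Step 3, effect on the test.** Suppose there is no true difference from withdrawal, 42 patients per arm, and a normal approximation. The shift in standard errors is c = (d/60) / (SD × √(2/42)), with d in minutes and SD in hours. The chance of a significant result is Φ(c − 1.96) + Φ(−c − 1.96). The SDs are assumed.

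| Difference in extubation | SD 2 h | SD 6 h | SD 12 h |
|---|---|---|---|
| 5 min | 5.4% | 5.1% | 5.0% |
| 10 min | 6.7% | 5.2% | 5.1% |
| 20 min | 11.9% | 5.8% | 5.2% |
| 30 min | 20.9% | 6.7% | 5.4% |

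Example: 20 min with SD 2 h gives c = 0.333 / (2 × 0.218) = 0.76, hence 11.9%. The 30 min row lies outside the 5 to 20 min range and is there only to show the trend. The nominal 5% is barely disturbed at SD 12 h, and is clearly exceeded only when the spread is about 2 h and the difference is 10 min or more. The calculation is symmetric in the sign of d.

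**Step 4, after the change.** With withdrawal of anesthetics as the origin, the subtracted term drops out and the shift is zero whatever d is.

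**The case against.** The strongest reply is that nothing is lost. Item 4 reports extubation time separately, so a reader sees any delay, and adding it to an item 6 time restores the time from withdrawal patient by patient. Extubation is a well-defined, recordable event, applied alike in both arms, and nobody drinks or walks before it. The outcomes are secondary and the likely shift is minutes against hours or days. Most of this stands and is why the point is minor. It does not rescue the definition, because the contrast defined in the protocol is the one that will be tested and reported, and readers of a published difference in time to first intake will not add the two back together.

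Three stronger readings are tempting, and the protocol supports none of them.

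- *That esketamine delays waking and so gains credit for it.* Section 1's remark on sedation compares esketamine with ketamine, not with saline, and the same section expects faster waking. Section 3.3 also adjusts propofol to the same BIS range in all patients. If waking is faster, the definition works against esketamine.
- *That the item 4 and item 6 results must move in opposite directions.* Only the shift has a fixed sign relative to item 4. The net item 6 difference also contains any true difference in event time. With extubation 10 min later and first flatus truly 3 h later, both outcomes would be worse with esketamine.
- *That a patient left intubated for many hours would have a poor recovery hidden.* The identity allows it, but nothing makes it likely here: patients are ASA I–II and aged 18 to 65, all go to the PACU, and section 3.2 removes those with severe complications affecting recovery or uncorrected hypercapnia.

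**Conclusion.** The point holds as a minor defect of definition. Three secondary outcomes start at an event after randomization that treatment may move and that is itself compared between arms, so any between-arm difference in extubation time enters all three with its sign reversed. That part is an identity and needs no assumption.

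Direction cannot be settled from the protocol. Size depends entirely on the assumed times and spreads: trivial for an outcome measured in days, and of possible consequence only for first intake or ambulation if these occur within a few hours or vary little between patients. QoR-15 at 24 h is timed from surgery, so the primary outcome and the sample size are untouched. A reader should not infer that the definition favors esketamine or that the item 6 results would be uninterpretable.

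**What to change.** In section 3.4 item 6, redefine the three durations to start at withdrawal of anesthetics, or at the end of surgery, using the same origin for all three. Withdrawal is the easier choice: item 4 already uses it, and section 3.3 ties it to completion of skin closure, a surgical step that does not depend on the patient's waking. Leave extubation time in item 4 as its own outcome.

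The cost is the wording of three definitions. Item 4 already requires the withdrawal and extubation times, so no new data are collected. For any patient already recorded under the present wording, adding extubation time to the item 6 value gives the time from withdrawal exactly.
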